## Methods

### Aims and objectives

#### Primary objectives

To determine the safety and efficacy of the watch and wait approach, by measuring the following endpoints in the watch and wait arm:Co-Primary endpoint 1: The ‘two-year local failure rate’Co-Primary endpoint 2: The rate of rectal preservation

Secondary objectives:To determine the safety of the watch and wait strategy by measuring the following endpoints (in the watch and wait arm):The ‘two-year local regrowth rate’The ‘two-year distant metastasis rate’The overall survivalThe ‘incurable disease-free survival rate’ (recurrent cancer that cannot be surgically excised with the intention of achieving a cure)Evaluate the role of biomarkersPlasma and tumour biopsy biomarkers (non-coding RNAs, methylated DNA), TILs, organoids and gut microbiome:i)To predict cCR (in both arms)ii)To identify residual disease, micrometastases and recurrence risk (in both arms)iii)As prognostic biomarkers (in both arms)Imaging biomarkers (mrTRG, diffusion and T2 signs)i)To predict sustained cCRPROMs (in both arms)Quality of life (quality of life and health related quality of life)Bowel related quality of lifeFear of cancer recurrenceSupportive care needsTo evaluate a defined monitoring schedule in the watch and wait armCost effectiveness analysis: (both arms)

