#### Registration

Subjects must meet all the inclusion criteria and none of the exclusion criteria to be eligible for this study. Subjects must be registered before entering the study. Registration should be done only after all screening assessments have been performed.

Run-in phaseParticipants receiving only CRT:i)Run-in phase post CRT – week 8–10: patients will have a clinical assessment and endoscopy (sigmoidoscopy) and CT scan (run-in investigations) between week 8—10 post CRT. If there is no evidence of residual cancer found in the run-in phase investigations, subjects will have an MRI.ii)Allocation visit – week 8–10: At the allocation visit all investigations during the run-in phase will be evaluated. Patients who have achieved cCR will be allocated into the watch and wait arm. All other patients will be allocated to standard management arm.Participants receiving TNT:i)Run-in phase post TNT – week 2–3: patients will have a clinical assessment and endoscopy and CT scan (run-in investigations) between week 2–3 after the last dose of TNT. If there is no evidence of residual cancer found in the run-in phase investigations, subjects will have an MRI. If patients are required or decide to stop the doublet chemotherapy earlier than the recommended number of cycles, they will proceed to tumour response assessment 2–3 weeks after the last dose of doublet chemotherapy and allowing a minimum of 8 weeks post CRT before the response evaluation takes place.ii)Allocation visit (participants receiving TNT) – week 2–3 after the last dose of doublet chemotherapy. At the allocation visit all investigations during the run-in phase will be evaluated. Patients who have achieved cCR will be allocated into the watch and wait arm. All other patients will be allocated to standard management arm.

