### Outcomes, endpoints and other measures

#### Safety and efficacy

Two-year local failure rate (Co-Primary Endpoint)This endpoint will be measured in the watch and wait arm only. It is defined as local recurrence (i.e., recurrence in the region of the rectum, mesorectum and adjacent lymph nodes) that cannot be resected with clear margins.Metastatic disease:Metastatic disease in the presence of local recurrence is considered ‘local failure’Metastatic disease in the absence of local cancer recurrence is not considered ‘local failure’The rate of rectal preservation (Co-Primary endpoint)This endpoint will be measured in the watch and wait arm only. It is defined as the rate of organ (rectal) preservation at two years.

Rate of incurable-disease free survival (incurable-disease or death)Defined as the interval from date of registration to the date of first evidence of ‘local failure’ or ‘distant metastatic disease’ or death, whichever occurs firstOverall survival (death from any cause)Overall survival is defined as the interval from the date of registration to date of death from any cause, or the date of last known follow-up alive.Two-year local recurrence rateLocal Recurrence is defined as evidence of recurrent disease within the pelvis, found by examination, endoscopy or imaging (CT or MRI). Biopsy and pathological confirmation are encouraged if technically possible and safe.Two-year distant recurrence rateDistant Recurrence is defined as evidence of recurrent disease other than local recurrence, found by imaging or on examination.

Translational research (biomarkers).

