### Statistical analysis

Analyses will include all patients enrolled. Local control will be assessed by the proportion, together with the 95% confidence interval, of patients not failing locally as their first event at 2 years. This proportion will be estimated using a competing risk cumulative incidence curve where distant failure or death prior to any failure is considered as a competing risk. This will be estimated in both groups.

Time-to event endpoints of progression free, local control and overall survival will be described using the method of Kaplan–Meier or cumulative incidence. Formal comparisons between groups will be performed using logrank, Cox proportional hazards, Gray and Fine & Gray methods. Exploratory comparative analyses include univariate and multivariate regression models for time-to-event outcomes, regression models for continuous outcomes and logistic regression analyses for binary outcomes. Other exploratory analyses will also be performed as appropriate. No imputation for missing data is envisaged which will be assumed to be missing at random. Quality of life will be summarized using trajectories over the follow-up time.

In the watch and wait arm: the study will be stopped if the number of cases with local failure reaches 3 cases in the first 15 participants, and 5 cases in the first 30 participants at 3 years based on the charts of Mehta and Cain. [55] (Table 3).

Study Committees.Trial management committee

The trial management committee will oversee study planning, monitoring, progress, review of information from related research, and implementation of recommendations from other study committees and external bodies (e.g., ethics committees).Independent safety and data monitoring committee

This study has an independent safety and data monitoring committee including experts in the field who are not involved in this study.

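### Local control is to be estimated in both groups, although local failure is defined for the watch and wait arm only and has no term for standard-arm tumour that is never cleared

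*Protocol article*

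**What the plan says.** **Where the endpoint is measured.** The Primary objectives section of the protocol article assesses safety and efficacy "by measuring the following endpoints in the watch and wait arm". The Safety and efficacy section repeats this for the two-year local failure rate: "This endpoint will be measured in the watch and wait arm only".

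**What the event is.** Local failure is "local recurrence (i.e., recurrence in the region of the rectum, mesorectum and adjacent lymph nodes) that cannot be resected with clear margins". A second local event, local recurrence, is defined in the same section as recurrent pelvic disease found on examination, endoscopy or imaging. The Secondary objectives also place the two-year regrowth rate in the watch and wait arm.

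**How it is analysed.** The Statistical analysis section takes all enrolled patients. It estimates the proportion "of patients not failing locally as their first event at 2 years" from a cumulative incidence curve in which "distant failure or death prior to any failure is considered as a competing risk". It then adds: "This will be estimated in both groups". The next paragraph lists local control with the time-to-event endpoints and announces formal group comparisons by logrank, Cox, Gray and Fine & Gray methods.

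**Who is in the other group.** Patients with a cCR go to watch and wait. For the rest, the Registration section states: "All other patients will be allocated to standard management arm".

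**The concern.** The two sections cannot both stand if they describe the same quantity. An endpoint measured in one arm cannot be estimated in two.

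The restriction to watch and wait also has substance, because the event fits that arm and does not fit the other. A watch and wait patient starts with no detectable tumour, so any later local disease is a regrowth and can be classified. A standard-arm patient starts without a cCR. Until the tumour has been cleared there is nothing to recur, and a tumour that is never cleared does not meet either local-event definition.

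At stake is the standard-arm local control figure and any between-group test that uses it. Local disease that cannot be cleared would be an event in one arm and, on the definitions given, no event in the other.

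**Working it through.** **1. The passages side by side**

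| Item | Safety and efficacy | Statistical analysis |
|---|---|---|
| Arm | Watch and wait only | Both groups |
| Local event | Recurrence not resectable with clear margins | Failing locally as first event; no separate definition |
| Persistent tumour | Not mentioned | Not mentioned; competing risks are distant failure and death only |

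The Statistical analysis section supplies no local event of its own, so the definitions in Safety and efficacy are the only ones available. The Gray and Fine & Gray methods are for competing risks, and local control is the only endpoint for which the section names a competing risk. The announced comparisons are therefore naturally read as including it.

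**2. Applying the definitions to a never-cleared standard-arm patient**

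- Local failure requires a recurrence: not met.
- Local recurrence requires recurrent disease: not met.
- Competing event: met only if distant failure or death occurs first.
- Otherwise no event is recorded, and the patient stays in the proportion not failing locally.

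A watch and wait patient whose regrowth cannot be resected with clear margins is recorded as a local failure.

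**3. Arm size (Sample size section)**

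- 47 / (1 − 0.05) = 49.5, rounded up to 50 in watch and wait.
- 50 / 0.20 = 250 enrolled.
- 250 − 50 = 200 in standard management.

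The plan's own figures reproduce. Only the 200 is needed here; one patient is 1/200 = 0.5 points.

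**4. Size of the overstatement**

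Let u be the share of the 200 whose tumour is never cleared, and r the share of the remainder with a counted recurrence. Ignoring competing events:

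- Control as written = 1 − (1 − u)r
- Control counting never-cleared patients as failures = 1 − (1 − u)r − u
- Difference = u, whatever the value of r

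The documents give neither u nor r for this arm. As assumptions, u is taken as 2%, 5% and 10%, and r as 5% for illustration.

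| u | Never cleared | Recurrences among the rest | Control as written | Control counting never cleared | Difference |
|---|---|---|---|---|---|
| 2% | 4 | 0.05 × 196 = 9.8 | 95.1% | 93.1% | 2 points |
| 5% | 10 | 0.05 × 190 = 9.5 | 95.25% | 90.25% | 5 points |
| 10% | 20 | 0.05 × 180 = 9.0 | 95.5% | 85.5% | 10 points |

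As written, the figure even rises slightly with u, because fewer patients remain who could have a recurrence. The differences are upper limits, since some never-cleared patients would have distant failure or death first.

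**The case against.** **The analysis may concern a different quantity.** The endpoint is called local failure and the analysis is called local control. The latter could be a broader supportive analysis, and Table 1 does schedule collection of outcome events in the standard arm from month 3 to month 24. This shows that a standard-arm estimate is feasible. It does not remove the conflict: this is the only analysis the article gives for the co-primary endpoint, and a separate quantity would still lack an event that fits the standard arm.

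**Event coding may be left to a fuller document.** Detailed coding commonly is. But the two sections differ on which arm is measured, and a later document could settle that only by overriding one of them.

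**The scoring is an inference.** This stands. No section says how an unresected or margin-positive standard-arm patient is coded. One can say only how such a patient would count under the definitions given.

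**The size rests on an assumed rate.** This also stands. Patients must be judged fit for surgery and T4 and metastatic disease are excluded, so the true share may lie at the low end of the range or below it. The arithmetic converts an assumption into points and does not estimate a bias.

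**Margin-positive resection need not be a failure.** Correct. Whether it counts is a choice of definition; what is needed is that the choice be stated.

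**Conclusion.** The point holds as a conflict between the endpoint definition and its analysis. Local failure is restricted to watch and wait in one section and estimated in both groups in another, and its definition has no place for standard-arm tumour that is never cleared. Under the only definitions given, standard-arm local control would be overstated by up to the never-cleared share: at most 2 to 10 points (4 to 20 of 200 patients) if that share is 2% to 10%. That range is an assumption.

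A reader might infer more than the documents support:

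- **That the co-primary result is biased.** It is not; watch and wait patients start from a cCR, and the definition works for them.
- **That watch and wait will look worse purely because of the scoring.** The groups are formed by response and so can differ in prognosis whatever the scoring. The net direction of an observed difference cannot be derived from the protocol.
- **That never-cleared patients are scored as controlled by rule.** No such rule is written.

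The point should be corrected, but it does not threaten the primary conclusion.

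**What to change.** **Preferred:** delete the sentence extending the estimate to both groups, and take local control out of the between-group comparisons. The Statistical analysis section then agrees with the endpoint definition and the Primary objectives.

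**Alternative:** keep a descriptive standard-arm estimate with its own event definition. State how persistent, unresected and margin-positive disease each count, and label the figure as not comparable with the first co-primary endpoint.

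**Cost:** one or two sentences in the analysis section, with no change to sample size or to the co-primary estimate. The downside is that the standard-arm figure is dropped or becomes less favourable.

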**Methods:**

Adult patients with a diagnosis of rectal cancer planned to receive neoadjuvant long course chemoradiotherapy (± subsequent combination chemotherapy) will be consented into the study prior to commencing treatment. After completing the chemoradiotherapy (± subsequent combination chemotherapy), based on the clinical response, subjects will be allocated to one of the following arms: subjects who achieved a clinical complete response will be allocated to the watch and wait arm and others to the standard management arm (which includes resection). The aim of the study is to determine the rate of local failure and other safety and efficacy outcomes in the watch and wait arm. Patient reported outcome measures and the use of biomarkers as part of the clinical monitoring will be studied in both arms of the study.

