## Background

Rectal Cancer is a common malignancy [1], comprising one third of all colorectal cancer cases [2]. In patients with non-metastatic locally advanced rectal cancer (stage II or III), the current standard management approach involves pre-operative (neoadjuvant) chemotherapy and radiotherapy followed by total mesorectal excision. Neoadjuvant chemoradiotherapy (CRT) is also recommended in patients with extramural vascular invasion (EMVI)—detected by magnetic resonance imaging (MRI)—as EMVI has been identified as a risk factor that predicts relapse, regardless of T and N stage.[3] Surgical resection of the rectum involves a mortality risk and can lead to considerable morbidity, including serious complications such as anastomotic leak.[4, 5] Other possible complications following rectal cancer resection include sexual and urinary dysfunction, which can occur in up to 25% of patients treated by radical surgery, even with meticulous nerve-sparing procedures and in highly specialized centres.[6].

Preoperative CRT can reduce the size of the primary tumour and the depth of tumour penetration and can potentially sterilize the involved lymph nodes. Large randomized studies have established preoperative CRT as the preferred treatment option for patients with stage II or III rectal cancer.[7–11] More recently, studies have shown that the addition of combination chemotherapy to either a short course of radiotherapy or standard long course concurrent CRT before surgery, can improve outcomes.[12–14] This approach is called total neoadjuvant therapy (TNT).

In some patients, preoperative CRT can lead to pathological complete response. Pathological complete response is established when no viable malignant cells are found in the resected surgical specimen. Patients who achieve pathological complete response have better outcomes.[15] Pooled analysis of data shows the rate of pathological complete response to be approximately 15% with CRT and 30% with TNT.[16] Establishing pathological complete response requires examination of the surgical specimen. In patients who have not had surgery, clinical complete response (cCR) is used as a surrogate for pathological complete response. cCR is established when no malignancy is found on clinical examination, imaging, endoscopy (sigmoidoscopy) and biopsy.[15, 17] Surgery may not be necessary in these patients. This approach is known as watch and wait.

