#### Cost effectiveness

To determine the cost effectiveness of the watch and wait approach, a within-trial economic evaluation from a healthcare sector perspective will be conducted using a cost-utility analysis (CUA), in which the effectiveness will be measured by quality-adjusted life-years (QALYs). The cost-utility analysis involves estimating the incremental cost effectiveness ratios (ICERs) of the watch and wait approach versus standard management plan. For the within-trial economic evaluation, only costs and effects that accumulate within the trial participation up to 24 months will be considered.

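### Arm is fixed entirely by clinical response, so the formal between-group tests and the whole-arm ICER contrast responders with non-responders and cannot estimate the effect of watch and wait

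*Protocol article*

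**What the plan says.** The allocation rule is deterministic. The Abstract (Methods) says that "subjects who achieved a clinical complete response will be allocated to the watch and wait arm and others to the standard management arm". The run-in text under Registration repeats it, for chemoradiotherapy alone and for total neoadjuvant therapy: "Patients who have achieved cCR will be allocated into the watch and wait arm. All other patients will be allocated to standard management arm".

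The Background treats response as prognostic: "Patients who achieve pathological complete response have better outcomes". It adds that, without a surgical specimen, "clinical complete response (cCR) is used as a surrogate for pathological complete response".

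Two analyses then set the arms against each other:
- Statistical analysis: "Formal comparisons between groups will be performed using logrank, Cox proportional hazards, Gray and Fine & Gray methods". The time-to-event endpoints named just before are progression-free survival, local control and overall survival. Exploratory comparative models come in a separate sentence, so the formal tests are not themselves labelled exploratory.
- Cost effectiveness: "The cost-utility analysis involves estimating the incremental cost effectiveness ratios (ICERs) of the watch and wait approach versus standard management plan", with costs and effects counted up to 24 months. The stated purpose is to establish the cost effectiveness of the approach, and the Discussion expects the result to inform health policy.

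The Discussion recognises that the ideal comparison is randomized, against surgery, among complete responders, and explains why it was judged unlikely to accrue. Its answer to selection bias is to enrol before chemoradiotherapy starts.

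**The concern.** A between-arm contrast estimates a management effect only if the arms would have had similar outcomes under the same management. Here they differ by construction in a factor that the protocol itself calls prognostic. A hazard ratio, a Gray test or an incremental QALY computed across the arms mixes how well the tumour responded with what was done afterwards.

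The two strategies are also not alternatives for the same patient within this study. Under the allocation rule non-responders do not enter watch and wait, and responders are not allocated to standard management. An ICER labelled as watch and wait versus standard management would still be read as the value of choosing one over the other. That is the result most likely to be used outside the trial.

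Enrolling before treatment makes the watch and wait cohort more representative of complete responders. It does nothing to make the two arms comparable.

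**Working it through.** **1. The plan's own figures.** Sample size section: 47 assessable, 5% dropout, 20% complete response.
- 47 / 0.95 = 49.5, rounded up to 50.
- 50 / 0.20 = 250 enrolled.
- 250 − 50 = 200 in standard management.

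These reproduce. They rest on one-arm precision and use no between-group effect, so nothing here changes them.

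**2. Overlap.** By the allocation rule, the planned share of complete responders is 1 in watch and wait and 0 in standard management. Adjustment for response needs both values in both arms. There are none, so the exploratory multivariate models cannot separate response from management, whatever covariates are chosen.

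**3. What prognosis alone can produce.** The documents give no prognostic hazard ratio, so these inputs are assumed: management effect zero, exponential times, censoring at 2 years, 50 versus 200 patients, two-sided 5% log-rank test (alpha is not stated), 4,000 simulated trials per cell. The entries are rejection rates.

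| 2-year event risk in non-responders | HR 1.0 | HR 0.7 | HR 0.5 | HR 0.3 |
|---|---|---|---|---|
| 10% | 4% | 5% | 12% | 28% |
| 20% | 5% | 10% | 30% | 67% |
| 30% | 5% | 18% | 49% | 87% |
| 40% | 5% | 23% | 64% | 96% |

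The spurious risk difference is p − [1 − (1 − p)^HR]. At HR 0.5 it is 0.10 − 0.051 = 4.9 points for p = 10%, and 0.40 − 0.225 = 17.5 points for p = 40%.

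**4. Overall survival, same logic.** Assume 2-year survival of 97% in responders and 92% to 94% in non-responders, from prognosis only.
- HR = ln(S1)/ln(S2): ln 0.97 / ln 0.92 = 0.37; ln 0.97 / ln 0.94 = 0.49.
- Life-years over 2 years = (1 − S)/λ with λ = −ln(S)/2: 1.970 for 97%, 1.919 for 92%, 1.939 for 94%. The differences are 0.051 and 0.030.
- Simulated log-rank rejection: about 16% (97% versus 92%) and about 5% (97% versus 94%).

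So the estimate is distorted in every case, but a significant test is not assured.

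**5. The direction can reverse.** The Background cites a series in which 28 of 90 watch and wait patients (31%) had local recurrence, 26 of them managed with salvage surgery. Suppose any regrowth counts as an event, 31% is taken as the 2-year risk (an assumption, since median follow-up in that series was 60 months), and the resected arm has an assumed 5% to 15%. The hazard ratio is then ln 0.69 / ln 0.95 = 7.2 down to ln 0.69 / ln 0.85 = 2.3, and the log-rank test favours standard management in more than 99% down to 73% of simulated trials.

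Surveillance pushes the same way. Table 1 schedules 8 sigmoidoscopies and 6 MRIs after allocation in watch and wait, against standard of care in the other arm.

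**The case against.** The best defence is that little of the study depends on these contrasts. Both co-primary endpoints, and the secondary safety endpoints of regrowth, metastasis, overall survival and incurable-disease-free survival, are set for the watch and wait arm alone. The sample size and the stopping rule are also single-arm. The design is called a longitudinal cohort study, the Discussion is open about why it is not randomized, and nothing says that the tests will be read as management effects. Covariates and economic methods may sit in a fuller plan. All of that stands and limits the severity. It does not remove the point: the tests are called formal, the ICER is described as measuring the approach, and no covariate list can supply the missing overlap.

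A reader might infer more than the documents support:
- **That a significant result favouring watch and wait is to be expected.** Steps 3 and 4 show low rejection rates when events are few, and step 5 shows that local control or progression could go the other way.
- **That the ICER will look favourable.** No cost figures are given, and 0.03 to 0.05 life-years alone does not settle it.
- **That the plan contradicts itself by restricting local failure to watch and wait while estimating local control in both groups.** The first is defined by recurrence that cannot be cleared surgically, and the second by local failure as first event. They may be different quantities.
- **That standard-arm patients with no residual tumour at resection supply the missing comparator.** They are identified only after surgery, and pathology excludes the occult residual disease that some watch and wait patients carry. One bias would replace another.

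**Conclusion.** The point holds for the between-group time-to-event tests and for the whole-arm ICER. As written, both contrast responders with non-responders and cannot estimate the effect of the management approach. This follows from the allocation rule and the protocol's own statement on prognosis. That statement concerns pathological response and is carried to clinical response by the surrogate argument.

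The size cannot be fixed from the documents. Under the stated assumptions, prognosis alone moves rejection from the nominal 5% to anywhere between about 5% and 96%, and at a hazard ratio of 0.5 it creates a risk difference of 4.9 to 17.5 points. For local control and progression the direction is not assured. The co-primary results are untouched, so this is something that should be fixed rather than a threat to the study's main conclusion.

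**What to change.** **Statistical analysis.** Replace the formal between-group tests with descriptive estimates by arm, with confidence intervals. State that differences between arms reflect response and management together. Keep Cox and Fine & Gray models for prognostic factors within an arm.

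**Cost effectiveness and Cost-utility analysis.** Report the whole-arm contrast in costs and QALYs as descriptive, and state that it does not estimate the cost effectiveness of watch and wait. Any base-case ICER should use an external or modelled comparator of clinical complete responders managed by surgery. Standard-arm patients with no residual tumour at resection can serve at most as a sensitivity analysis, labelled with the selection problem described above.

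**Cost.** The first change is wording only, and the study gives up a formal between-arm p-value. The second needs external or modelled inputs, so the ICER will carry wider uncertainty. Neither changes enrolment, visits or the primary analysis, and both are best made before outcome data are seen.

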### Design

This is a Longitudinal Cohort Study.

Eligible subjects, after consent/registration, will complete CRT and then based on response will be allocated to one of the two study arms.

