## Discussion

In this study we are aiming at investigating the safety of the watch and wait approach in patients who achieve cCR after CRT for locally advanced rectal adenocarcinoma. The current study will add to accumulating data from previous retrospective series and ongoing prospective studies. We will investigate a multitude of biomarkers to assess their role in predicting response or treatment failure. This will help identify the group of patients who benefit from this approach. This study investigates a comprehensive set of PROMs and helps understand the watch and wait approach from the patients’ perspective. We will investigate the cost effectiveness of the treatment; the findings will help guide health policy. Finally, this study will help establish a structured follow up protocol for patients managed by the watch and wait approach in the future.

Retrospective studies of the watch and wait approach are prone to selection bias. The ideal study design to avoid this is a randomized study comparing the watch and wait approach with standard treatment (surgery) in patients who achieve complete response; however, randomizing patient to a surgical approach versus non-surgical management is challenging and is unlikely to accrue the required number of patients. To avoid selection bias, we have elected to enrol the participants into the study prior to starting CRT: the watch and wait approach is offered to the participant who achieve cCR. This way we are aiming to reduce the selection bias.

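### The planned formal between-arm survival tests compare responders with non-responders and cannot estimate the effect of omitting surgery (correction to a secondary analysis)

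*Protocol article*

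**What the plan says.** **How the arms are formed.** The Design section says "This is a Longitudinal Cohort Study"; there is no randomisation. The allocation rule under Registration is: "Patients who have achieved cCR will be allocated into the watch and wait arm. All other patients will be allocated to standard management arm". The Methods paragraph of the abstract gives the same rule.

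**What response means for prognosis.** The Background says "Patients who achieve pathological complete response have better outcomes" and describes clinical complete response (cCR) as the surrogate used when there is no surgical specimen.

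**What is analysed.** Under Statistical analysis, "Time-to event endpoints of progression free, local control and overall survival will be described using the method of Kaplan–Meier or cumulative incidence", and then "Formal comparisons between groups will be performed using logrank, Cox proportional hazards, Gray and Fine & Gray methods". Exploratory comparative analyses are listed separately in the next sentence, so these tests are not among them. All enrolled patients are analysed. Under Outcomes, endpoints and other measures, overall survival runs from the date of registration, which precedes chemoradiotherapy and allocation.

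**What is asked.** Under Aims and objectives, overall survival and the other safety endpoints are to be measured in the watch and wait arm. The Discussion describes the ideal study as a randomised one "comparing the watch and wait approach with standard treatment (surgery) in patients who achieve complete response", judges it unlikely to accrue, and relies on enrolment before chemoradiotherapy to limit selection bias.

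**The concern.** Group membership is itself an outcome of the neoadjuvant treatment. Under the stated rule no responder is planned for surgery and no non-responder for watch and wait. A logrank, Cox, Gray or Fine & Gray contrast of these groups mixes whatever omitting resection does with the prognosis that goes with response, and nothing in the data can separate the two. Enrolling before chemoradiotherapy limits selection into the cohort, but it does not make the two arms comparable.

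The study's stated purpose is to establish safety. A significant overall survival result in favour of watch and wait could be cited as evidence that leaving the rectum in place is safe, although it could arise wholly from response. The article attaches no caveat, restriction or allocation-based time origin to the comparison.

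**Working it through.** **1. The plan's own figures.** From Sample size: 47/(1 − 0.05) = 49.5, rounded up to 50 watch and wait patients; 50/0.20 = 250 enrolled; 250 − 50 = 200 in standard management. These reproduce. No effect size or power is stated for the between-arm tests.

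**2. Why adjustment cannot help.** Let A = 1 for watch and wait and R = 1 for cCR at allocation. The rule sets A = R for every patient. In a Cox model with log hazard βA + γR plus baseline covariates, only β + γ can be estimated. If strategy has no effect (β = 0), the fitted arm hazard ratio is exp(γ), the prognostic effect of response. The same aliasing holds in a Fine & Gray model.

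**3. Size for overall survival.** The protocol gives the direction of γ but no survival figures by response, so the rates below are assumptions. Set-up: 50 v 200 patients, exponential times, censoring at two years, two-sided 5% logrank test, no effect of strategy. Hazard ratio = ln(S_WW)/ln(S_std). Expected deaths = 50(1 − S_WW) + 200(1 − S_std).

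| Assumed two-year survival, WW v standard | Hazard ratio | Expected deaths | Significant and favouring WW |
|---|---|---|---|
| 95% v 95% | 1.00 | 2.5 + 10 = 12.5 | 0.6% (about 4% in either direction) |
| 95% v 90% | 0.0513/0.1054 = 0.49 | 2.5 + 20 = 22.5 | about 14% |
| 97% v 88% | 0.0305/0.1278 = 0.24 | 1.5 + 24 = 25.5 | about 45% |
| 98% v 90% | 0.0202/0.1054 = 0.19 | 1 + 20 = 21 | about 45% |

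The nominal rate in one direction is 2.5%. Separate runs agree to within about three percentage points. A wider grid shows the dependence on the inputs: with a responder hazard ratio of 0.5, the rate is 13%, 31%, 47% and 64% for standard-arm two-year event rates of 10%, 20%, 30% and 40%; with 0.3 it is 28%, 68%, 88% and 96%. Schoenfeld's formula gives higher values (26% at hazard ratio 0.5 and a 10% event rate). With about 22 events the simulation is the safer guide.

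**4. The time origin.** A patient must be alive at allocation to enter watch and wait, but the clock starts at registration. This check gives all patients the same hazard, makes response independent of outcome, and counts patients who die before allocation in the standard group (an assumption, since the article does not place them).

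| 24-month event rate | Mean rate ratio, allocation at 3.5 months | Mean rate ratio, allocation at 8 months |
|---|---|---|
| 10% | 0.90 | 0.69 |
| 20% | 0.87 | 0.66 |
| 30% | 0.84 | 0.65 |

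The 3.5 months fits chemoradiotherapy alone: 25 fractions, assumed five a week, is 5 weeks; 5 + 10 = 15 weeks, or about 3.5 months. For total neoadjuvant therapy, 5 + 2 + (6 × 3) + 3 = 28 weeks, about 6.4 months, so 8 months is an outer value that allows for delays.

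**5. Local control and progression-free survival.** A retained rectum can regrow. The Background reports local recurrence in 28 of 90 watch and wait patients (31%). If regrowth counts as an event, 31% in 50 patients against an assumed 5%, 10%, 15% or 20% in 200 gives power of 99%, 93%, 72% or 40% for a difference **against** watch and wait. The 31% comes from a median follow-up of 60 months, so a two-year figure could be lower. If local control instead means unresectable failure, the article defines that endpoint for the watch and wait arm only, and the direction of a between-arm contrast is not settled.

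**The case against.** The strongest reply is that nothing important depends on these tests. Both co-primary endpoints are measured in the watch and wait arm only, the sample size rests on single-arm precision, and the stopping rule is single-arm. The survival objectives are also confined to that arm. The article calls the study a cohort, acknowledges that randomisation among complete responders would be the ideal, and nowhere claims that the comparisons estimate the effect of omitting surgery. Responder v non-responder survival is a legitimate prognostic description. All of this stands. It limits the point to a secondary analysis and makes relabelling an acceptable alternative to deletion. It does not rescue a contrast called formal, carried out between arms named after management strategies, with no statement of what it estimates.

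A second reply is that the size is assumed. This also stands: the protocol supplies no survival rates by response, and the milder assumption of 95% v 90% brings the figure down to about 14%. That is still well above 2.5%.

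Two stronger readings are tempting. A reader might infer that every time-to-event endpoint will favour watch and wait. The documents support that direction only for overall survival, since the reported 31% recurrence could turn local control or progression-free survival the other way. A reader might also infer that the fault undermines the trial's main conclusion. The single-arm co-primary endpoints show that it does not.

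**Conclusion.** The point holds as a correction to a secondary analysis. The planned tests cannot estimate the effect of omitting surgery on any endpoint. This follows from the allocation rule alone and needs no numerical assumption.

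The direction is supported for overall survival only. It rests on the protocol's statement about pathological complete response and its use of cCR as the surrogate. The registration time origin adds to it if deaths before allocation are counted in the standard group. The rate of about 14% to 45% rests on assumed two-year survival, exponential times, complete two-year follow-up and the planned 50 v 200 split. It illustrates the size of the problem and is not a forecast.

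**What to change.** In Statistical analysis, delete the formal between-arm tests and hazard ratios for the time-to-event endpoints, or relabel them as descriptive, non-causal contrasts of responders with non-responders. Report each arm separately with 95% confidence intervals, and state that the arms are not comparable because response determines allocation. Start any curves shown side by side at the allocation visit.

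Standard-arm patients with a pathological complete response, timed from allocation, should not be used as a comparator. They are identified only after resection, so they are guaranteed to survive to surgery. They were also judged not to have cCR at allocation, so they do not supply the contrast that the Discussion describes.

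The change is one of wording. It gives up between-arm p-values that cannot be interpreted, and it leaves the co-primary endpoints, sample size and stopping rule as they are.
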